#### Procedure

We will access the sample through the same channels as in phase 1. First, we will explain the benefits of the project to the organizations and request their support in encouraging their patients to participate. The directors of these organizations will receive the link to the web-based questionnaire, which will then be distributed to patients who, for security reasons, can only complete the questionnaire at the respective facilities.

Participants willing to participate will have to complete a web-based questionnaire. The first page will outline the objectives of the study, and the second page will ask participants to confirm whether they meet the inclusion criteria, as described in the phase 1 Procedure subsection. Specifically, participants must be women aged ≥18 years and must have been living with one of the identified types of CP for at least 3 months.

Participants will have 1 month to complete the questionnaire. During this period, answers will be saved in the system to allow participants to complete the questionnaire on different occasions; however, as stated, the professionals at the centers will need to activate the survey links. Survey links are deactivated to prevent respondents from completing the questionnaires outside of the designated locations. The data will be automatically stored in a database, and the progress of sample collection will be monitored weekly to ensure that each group reaches the necessary sample size.

#### Variables and Instruments

The variables and instruments that will be used, organized by purpose, are summarized in Table 2 and described in the subsections that follow. Some response scales will be alternated to identify biases in participants’ responses.

**Table 2 table2:** Variables and instruments used in study 2, organized by purpose.

Variable	Questionnaire	Control purposes^a^	Data analysis
Chronic pain	1 screening item	✓	
Sociodemographic characteristics	Ad hoc questionnaire	✓	✓
Access to the study	Ad hoc question	✓	
IPV^b^ against women	European Union Agency for Fundamental Rights study on violence against women survey inventory		✓
Possible traumatic events experienced	Adapted version of Life Events Checklist for DSM-5	✓	✓
Disabling chronic pain	GCPS-R^c^		✓
Severity of PTSD^d^ symptoms	EGS-R^e^		✓
Gender norms and gender identity	CFNI-45^f^		✓
Activity patterns	APS^g^		✓
Exercising	IPAQ^h^		✓
Pain worrying (pain catastrophizing)	PCS^i^		✓
Pain-related self-efficacy	CPSS^j^		✓
Informal social support	ISSADI-PAIN^k^		✓
Health related quality of life	MOS SF-12^l^		✓
Physical functioning	BPI- SF^m^		
Anxiety and depression	HADS^n^		✓
Suicide attempts and thoughts	Ad hoc questionnaire		✓
Medication use and illegal drug use	Ad hoc questionnaire		✓
Health service use	Ad hoc questionnaire		✓

^a^We include compliance with the inclusion and exclusion criteria.

^b^IPV: intimate partner violence.

^c^GCPS-R: Graded Chronic Pain Scale Revised.

^d^PTSD: posttraumatic stress disorder.

^e^EGS-R: Escala de Gravedad de Síntomas Revisada (Posttraumatic Stress Disorder Symptom Severity Scale-Revised)

^f^CFNI-45: Conformity to Feminine Norms Inventory-45.

^g^APS: Activity Patterns Scale.

^h^IPAQ: International Physical Activity Questionnaire.

^i^PCS: Pain Catastrophizing Scale.

^j^CPSS: Chronic Pain Self-Efficacy Scale.

^k^ISSADI-PAIN: Informal Social Support for Autonomy and Dependence in Pain Inventory.

^l^MOS SF-12: Medical Outcomes Study Short-Form Health Survey-12.

^m^BPI-SF: Brief Pain Inventory–Short Form.

^n^HADS: Hospital Anxiety and Depression Scale.

#### Variables and Instruments for Control Purposes

### Screening for CP and Type and Sociodemographic Characteristics

These variables are described in detail in the phase 1 CP and Type and Sociodemographic Characteristics subsections.

### Access to the Study

Participants will have to indicate how they accessed the study (associations and support centers for IPV against women, CP associations, CP units, or primary health care centers).

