#### Procedure

First, we will reach out to the organizations through which we plan to access both groups and request their collaboration. To contact women who have experienced or are experiencing IPV and women with CP, we will consult associations and support centers for IPV against women, CP associations, CP units, and primary health care centers. These organizations will be asked to inform their patients about the project and encourage their participation.

Eligible candidates will be required to complete a series of questionnaires (refer to the Instruments subsection) to determine whether they meet the inclusion and exclusion criteria. The data from those who do not meet the criteria will be discarded. Those who qualify will proceed to complete additional questionnaires. The answers from these questionnaires will help us form the 2 groups while ensuring diversity based on age, racial background, and degree of disabling CP.

The inclusion criteria for both groups will be as follows: (1) women aged ≥18 years, (2) in a heterosexual intimate relationship for at least 1 year (as per Spanish law, IPV against women pertains to violence perpetrated by male intimate partners) [15], and (3) living with a CP condition highly prevalent in women and among those who have experienced IPV against women (eg, fibromyalgia, abdominal pain, genitourinary tract pain, pelvic and genital pain, headaches [including migraines], back and neck pain, and chronic fatigue syndrome) [19-22]. Women belonging to group 1 will, in addition, have to be currently experiencing IPV.

The exclusion criterion for group 2 will be having previously experienced IPV against women or any other form of violence because this may affect their current intimate relationships. The exclusion criterion for both groups will be experiencing oncological pain.

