#### Sample Size Calculation

To calculate the sample size, the prevalence of the pain-avoidance activity pattern was used, which is typically present in cases of highly disabling CP [102]. Specifically, we considered several factors: first, the expected prevalence ratio assumed to be 2.0 between individuals with CP who are exposed to IPV against women and those who are not. Second, we estimated the prevalence of the pain-avoidance activity pattern within the study population, assuming it to be approximately 20%. While a previous study found that 40.4% of patients with fibromyalgia exhibited this pattern [133], we decided to use a more conservative estimate, given that the prevalence of this behavior is likely lower among the broader population of patients with CP. Finally, we accounted for the expected prevalence of IPV exposure among women with CP, estimated at 30% based on findings from earlier research [23].

We have defined the risk level α as 5% and the study power as 90%. The program used for size calculation was a macro, !NSize, for SPSS Statistics [134]. On the basis of these parameters, the required sample size consists of 359 women with CP: 193 (53.8%) with CP alone, 83 (23.1%) with CP and a current history of IPV, and 83 (23.1%) with CP and a past history of IPV.

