#### Data Analysis

Inferential statistics help researchers draw conclusions about populations based on sample data, providing insights into social phenomena [153]. Machine learning, as a subset of artificial intelligence (AI) techniques, analyzes large datasets to identify patterns and make predictions [154]. These methods are transformative in gender studies, uncovering patterns in gender-related data and deepening the understanding of social inequalities and biases [155]. These methods have been successfully applied to areas such as forecasting gender-based violence, further demonstrating their relevance in social sciences [156].

Exploratory data analysis (EDA) will be crucial in examining CP and its connection to past or current IPV against women. EDA uses techniques such as scatterplots, clustering algorithms, and principal component analysis to investigate multidimensional datasets [157]. Scatterplots help identify correlations between sociodemographic variables, clustering algorithms reveal subgroups within the population, and principal component analysis reduces dimensionality to uncover latent factors such as the relationship between gender identity and social support [158]. The use of EDA will allow us to detect groups and subgroups at a glance by creating subclusters, that is, more specific profiles in each of the groups.

Inferential statistical methods will be applied to differentiate between women with CP alone and those with CP who have experienced IPV in the past or are currently experiencing IPV. Hypothesis testing, estimation, and prediction techniques will be used to make comparisons, with visual tools such as boxplots for examining variable distributions across groups. We will use 2-tailed *t* tests and ANOVA to compare means across groups [159].

Feature ranking techniques will help identify the most relevant variables for accurate classification. Methods such as information gain, gain ratio, Gini index, and relief will determine the importance of features such as education, socioeconomic status, pain level, and social support [160]. This feature ranking will help prioritize the most influential factors affecting each group, including those based on country distribution.

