### Limitations

This study is not without limitations. One of the main challenges is the high number of participants required for the quantitative study. To mitigate this issue, we will contact primary health care centers, associations and support centers for IPV against women, CP associations, and CP units across the province of Alicante. A second limitation is the use of nonprobability sampling, which may introduce bias. However, this research aims to provide a preliminary understanding of the co-occurrence of these 2 significant health issues; to the best of our knowledge, it will be the first to do so with a large sample using AI. A third limitation concerns the number of questionnaires that need to be completed in the second study. To address this, participants’ responses will be saved, and they will be given ample time to complete all questionnaires. In addition, the order of presentation will be randomized to reduce the likelihood that the same questionnaires are consistently left unanswered. We hope this will result in a similar number of responses across all questionnaires. To further encourage questionnaire completion, we will ask the center directors and professionals to remind participants about the importance of answering all questions.

A fourth limitation is the focus on only individual and relational factors. While community and societal factors also influence CP and its disabling effects [168], the primary aim of this study is to enhance the detection and treatment of CP in health care settings by personalizing care. Therefore, the focus is placed on individual and relational factors. Finally, not all scales have been validated with Spanish samples. Validating several scales has high costs and is time consuming, but we will conduct translation and back-translation procedures and test the instruments directly with the population. Moreover, the study will only be conducted in the province of Alicante. However, if profiles are identified, we plan to extend the second study to other Spanish regions as well as other countries while controlling for other macrovariables (eg, free access to the health system) to analyze the commonalities and differences in the profiles. If minimal or no differences are found, the profiles could be largely explained by the experience of IPV against women, and recommendations could be generalized to similar countries.

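### Phase 2 compares the groups with crude tests, although one recruitment channel can supply almost no CP-alone women, and the recorded channel has no stated role in the analysis

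*Protocol article*

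**What the plan says.** Phase 2 uses the phase 1 channels. The phase 1 Procedure lists them: "we will consult associations and support centers for IPV against women, CP associations, CP units, and primary health care centers". All groups share this one list, and no channel is assigned to a group. The phase 2 Procedure provides weekly monitoring so that each group reaches its size; it states no balance of channel across groups.

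Under phase 2 Participants, the CP-alone group is limited to women who have never experienced IPV or any other violence.

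The channel is collected: "Participants will have to indicate how they accessed the study" (Access to the Study). Table 2 ticks this variable under control purposes and leaves its data-analysis cell blank. The footnote to the control column mentions compliance with the eligibility criteria.

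For the group comparison, phase 2 Data Analysis names two-tailed t "tests and ANOVA to compare means across groups". It then describes feature ranking, classifiers and Shapley values. It mentions no covariate, stratification, matching or sensitivity analysis by channel.

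The Limitations section concedes the general point: "A second limitation is the use of nonprobability sampling, which may introduce bias". It names no analytic remedy.

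**The concern.** Eligibility for the CP-alone group ties channel to group. A woman reached through an IPV support center will almost always belong to one of the two IPV groups. If those groups fill slowly, support centers are a natural place to find more women, and that widens the imbalance.

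Channel is also likely to be related to the outcomes. Pain units may select for disabling pain and medication, and support centers for distress. Health service use is measured as general practitioner visits, while primary care is itself a channel. The bias can go either way: CP-alone women drawn from pain units could mask greater disability in the IPV groups, and IPV women drawn from support centers could show more distress for reasons of source.

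The classifiers do not solve this. They predict group membership, so a feature that marks where women were recruited can rank high as a feature of IPV. At stake is specific aim 5, which asks which factors best explain the group profiles. Repeating the same recruitment in other regions, as the Limitations section foresees, could reproduce the same pattern, so agreement across regions would not rule it out.

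**Working it through.** **1. The plan's own sample size.** Sample Size Calculation gives α = 5%, power 90%, "the expected prevalence ratio assumed to be 2.0 between individuals with CP who are exposed to IPV against women and those who are not", a pain-avoidance prevalence of about 20%, and IPV exposure "estimated at 30% based on findings from earlier research". Take 20% vs 40%, two-sided, exposed to unexposed 3:7.
- Standard two-proportion formula without continuity correction: 177 + 76 = 253.
- With continuity correction: 193 + 83 = 276.
- Adding a second IPV group of 83: 276 + 83 = 359, the stated total.

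The plan's figure reproduces exactly, as a crude comparison with no allowance for channel or covariates.

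**2. Spurious difference on a continuous outcome (assumed inputs, no true IPV effect).** Bias = difference in channel mix × channel effect. For one IPV group against CP alone, SE = √(1/193 + 1/83) = 0.131 SD. The probability of a significant result is Φ(bias/SE − 1.96) + Φ(−bias/SE − 1.96).

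| Mix difference | Channel effect | Bias | Bias/SE | P(significant) |
|---|---|---|---|---|
| 50 points | 0.5 SD | 0.25 SD | 1.90 | 48% |
| 50 points | 0.3 SD | 0.15 SD | 1.14 | 21% |
| 20 points | 0.3 SD | 0.06 SD | 0.46 | 7% |

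**3. The same on the sample-size endpoint (assumed inputs).** Let the pain-avoidance prevalence be 20% in one type of channel and 40% in another, with no IPV effect within either. A group's apparent prevalence is 0.20 + 0.20 × its share from the second type.

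| Share, CP alone vs IPV | Apparent prevalence | Ratio | P(significant), 193 vs 83 |
|---|---|---|---|
| 30% vs 50% | 26% vs 30% | 1.15 | about 11% |
| 20% vs 60% | 24% vs 32% | 1.33 | about 29% |
| 10% vs 80% | 22% vs 36% | 1.64 | about 67% |

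With channel prevalences of 20% and 30%, the ratios run from 1.09 to 1.33 and the rejection rates from about 6% to 25%.

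**4. Price of adjustment.** To keep precision after adjusting for a two-level channel, the pairwise N grows by 1/(1 − R²). Here R² = w(1 − w)(b − a)²/[p(1 − p)], w = 83/276 = 0.301, a and b are the two groups' shares, and p = (1 − w)a + wb.
- 30% vs 50%: R² = 0.04, N about 287.
- 20% vs 60%: R² = 0.16, N about 327.
- 25% vs 75%: R² = 0.22, N about 353.
- 0% vs 50%: R² = 0.41, N about 469.

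In the last case one channel has no CP-alone women at all, so adjustment there rests on the model and not on data.

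**5. Price of restriction.** If, say, half of an IPV group of 83 came from support centers and all 193 CP-alone women from the other channels, about 42 would remain. SE = √(1/193 + 1/42) = 0.170 SD, against 0.131 SD.

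**The case against.** Four arguments on the other side carry weight.

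- **Channel separation.** A reader might infer that the groups come through different channels, with IPV women mainly from support centers. The article does not say so. Its Background cites a rehabilitation-center study of 108 male and female CP patients in which 56% had current or past IPV and nearly 30% had IPV within the previous year. Pain settings could therefore supply many IPV women. Only the near absence of CP-alone women from support centers follows from the text.
- **Table 2.** A reader might infer that the authors decided to ignore channel. The control column may mean more than eligibility, since channel is not an eligibility criterion, and the Life Events Checklist, ticked in the same column, is meant to help control for outside traumatic events. The blank cell is weak evidence too: physical functioning (BPI-SF) is also blank, although it is a hypothesized outcome. The point rests on Data Analysis, which describes no method of control.
- **Detail left out of an article.** Covariate lists are often left to a fuller plan. That is fair for the covariates, but the article itself names crude comparisons and gives channel a non-analysis role.
- **Interpretation.** A reader might infer that differences will be presented as effects of IPV. The article calls the work preliminary, admits sampling bias, and attributes profiles to IPV only conditionally, after extension to other regions and countries. "May be read" is as far as the text allows.

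Adjusting the main analysis for everything collected is also open to challenge. Income, pain type and time since diagnosis may be affected by IPV, and adjusting for them could remove part of the difference of interest.

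**Conclusion.** The point holds in limited form. Channel is partly tied to group by the definition of CP alone, the named group comparisons are crude, and no described analysis uses the recorded channel. Source differences may therefore be mistaken for differences by IPV, in either direction.

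The size cannot be stated, because the documents give neither the channel mix nor any channel effect on the outcomes. Across the assumed scenarios the false-positive rate runs from about 6%, close to nominal, to about 67%. The 48% and 21% figures are correct arithmetic on assumed inputs and do not predict this study's result. The documents support neither complete separation of channels nor a known bias. The change is still worth making, because it uses data already collected and bears directly on what can be concluded about IPV.

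**What to change.** 1. Mark the access variable for data analysis in Table 2, and state in Data Analysis how it will be used.
2. Report a table of the three groups by recruitment channel.
3. Beside the crude results, repeat the group comparisons and the classifiers in women from channels that can supply all groups (CP units, CP associations, primary care), leaving out IPV support centers.
4. Within those channels, add a regression of each outcome on group, adjusted for channel and age.
5. Keep covariates that IPV may itself affect (income, pain type, time since diagnosis) for a sensitivity model.

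The cost is analysis wording and lower precision, with no new data. The loss depends on how many IPV women come from support centers and may be more than slight. The restricted comparison also describes IPV women reached outside support centers, a narrower population, which is why it should stand beside the crude results and not replace them.

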#### Variables and Instruments for Risk and Protective Factors

### Sociodemographic Characteristics

Age, belonging to a minority group (yes or no), years of education, annual household and personal incomes (categorized as €0 to €19,000; €20,000 to €40,000; and >€40,000; 1€=US $1.14), relationship status (single, partnered, or married), relationship duration (years), relationship satisfaction (10-point scale), CP diagnosis (yes or no), and time since CP diagnosis (years).

### Gender Norms and Identity

Gender norms and identity will be measured using the Conformity to Feminine Norms Inventory-45 [135,136]. The Spanish-adapted version of the inventory [137] consists of 23 items rated on a 4-point response scale ranging from 0=*strongly disagree* to 3=*strongly agree*. The inventory includes 7 subscales: care for children, invest in appearance, domestic, romantic relationship, nice in relationships, thinness, and modesty. It is designed to assess the degree to which women conform to traditional femininity norms as reflected in their behaviors, feelings, and thoughts. Higher scores on this inventory indicate a greater adherence to these traditional femininity norms. The Conformity to Feminine Norms Inventory- has demonstrated good psychometric properties, making it a reliable measure for evaluating conformity to feminine norms.

### IPV Against Women: European Union Inquiry; Possible Traumatic Events Experienced: Adapted Version of Life Events Checklist for DSM-5; Disabling CP: Graded CP Scale Revised; Severity of PTSD Symptoms: Posttraumatic Stress Disorder Symptom Severity Scale-Revised

These scales have been described in study 1. With regard to the IPV against women questionnaire, participants will have to indicate whether they are currently experiencing such situations or have experienced them in the past and for how long. In addition, those women who have experienced IPV in the past will be asked how long they have lived free from violence.

#### Activity Patterns: Activity Patterns Scale

### Overview

The 3 activity patterns—pacing, avoidance, and persistence—can serve different goals and have varying impacts on health outcomes. To measure these patterns, we will use the Activity Patterns Scale [138]. This scale consists of 8 subscales, each with 3 items, for a total of 24 items. The subscales include pain avoidance, activity avoidance, task-contingent persistence, excessive persistence, pain-contingent persistence, pacing to increase activity levels, pacing to conserve energy for valued activities, and pacing to reduce pain. Participants will rate how well each statement applies to them on a 5-point scale ranging from 0=*not at all* to 4=*always*. Higher scores in a subscale indicate a stronger tendency to display the corresponding activity pattern. The instrument demonstrates adequate reliability as well as structural, convergent, and criteria validity. It has been specifically developed for use with the Spanish population [138].

### Exercising: International Physical Activity Questionnaire

Although some studies advocate the use of objective measures of physical activity and physical exercise [139], the International Physical Activity Questionnaire (IPAQ) [140] allows the collection of detailed information on physical activity performance comparable to that collected with objective measures such as pedometers [141]. The short, self-administered version of the IPAQ focuses on the past 7 days and consists of 7 items that estimate the time spent on moderate to vigorous physical activity, such as walking, bicycling, or heavy lifting, in at least 10-minute bouts over the week. This version provides a continuous score reflecting the minutes of physical activity performed, with higher scores indicating greater physical activity. The IPAQ presents good psychometric properties and is available in Spanish [140].

